### Lung function testing by spirometry

Spirometry prior to bronchodilation will be performed in line with ATS/ERS recommendations [40]. Subjects will sit while wearing nose clips, and the EasyOne Worldspirometer (ndd, Zurich, Switzerland) will be used to obtain flow-volume curves. To obtain optimal flow-volume curves, the participants perform at least three, but no more than eight, manoeuvres under the guidance of specifically trained and experienced examiners. All tests will be visually inspected by experienced physicians according to the ATS/ERS acceptability criteria [40]. Spirometric indices will be taken from the manoeuvre with the largest sum of forced expiratory volume in 1 s (FEV_1_) and forced vital capacity (FVC). Further parameters evaluated will be the ratio of FEV_1_ and FVC (FEV_1_/FVC), and the mean flow rate between 25 and 75% of FVC (FEF_25–75_). Standardized *z*-scores of the lung function parameters FEV_1_, FVC, FEV_1_/FVC and FEF_25–75_ will be calculated based on the reference equations for spirometry from the Global Lung Initiative (GLI—http://www.ers-education.org/guidelines/global-lung-function-initiative.aspx, [48]. After completion of baseline spirometry, subjects will inhale bronchodilator medication according to the ATS/ERS recommendations [40]. Two puffs (each 100 µg) of salbutamol will be delivered into a spacer (volumatic) by a metered-dose inhaler, and the participant will be asked to take five slow and deep breaths over 5–10 s for optimal deposition. Spirometry will be repeated 15 min after salbutamol inhalation. This analysis uses post-bronchodilator lung function data. A positive response is defined as an increase by > 12% and > 200 ml in FEV_1_ and/or FVC post-bronchodilation compared to pre-bronchodilation, according to ATS/ERS standards [40].

Specific attention will be paid to the requirement to obtain very precise and reliable lung function data. In addition to strictly following ATS/ERS recommendations, we will reach the goal of high-quality lung function testing by experienced and well-trained study nurses, the additional visual control by a pulmonologist and the repetition of tests for each subject. There is long-standing, well-documented expertise on lung function assessment in the investigators involved in this study.

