### Objectives {7}

The main objective is to test the hypothesis that gingivitis reduction via optimized daily oral hygiene and antibacterial chlorhexidine-containing (CHX) mouth rinsing improves lung function in terms of forced vital capacity (FVC), as an indicator of lung volume, by at least 2%. This allows interpreting the changes in lung function as direct or indirect consequences of changes in oral inflammation.

As a secondary objective, we test the hypothesis that gingivitis reduction by improved oral hygiene and CHX mouth rinsing improves forced expiratory volume in 1 s (FEV_1_) and forced expiratory flow rate at 25–75% of lung volume (FEF_25–75_), as indicators of airway obstruction, by at least 2%. Compared to the change in FVC, this will also allow to detect potential improvements regarding airway obstruction in terms of their ration FEV_1_/FVC. This is helpful for the interpretation of an improvement in lung function as a factor linked to a lower risk for obstructive airway disease.

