The power analysis focuses on the second part of the study, in which two different treatments are realized, whereby in both arms assessments before and after treatment are performed (Fig. 4). As the control treatment may be expected to be associated with a positive change, although smaller than in the target treatment group, the assumed effect is taken to be greater than zero. Thus, relative effects of m1 = 2 and of m2 = 1 are assumed for the target treatment and the control treatment group, respectively, in units that can be adapted to those of the outcome measures. There are no sufficient data on the (longitudinal) variation of measured values due to either methodological or biological sources. The power analysis is performed with an assumed variance of 1.5 for each assessment, in units identical to those of the effects and corresponding to a standard deviation (SD, square root of variance) greater than 1 but less than 1.5, which we consider as a reasonable value. Assuming that the measurement errors are independent in the pre and post-assessments, the variances add up for the pre-post differences, resulting in a total variance of each of the two differences of 3, i.e. an assumed standard deviation of about 1.7 (square root of 3) for each difference. Thus, we have two groups with expected effects of 2 or 1, both with standard deviations of about 1.7. This seems a reasonable basis for analysis, whereby the mean differences observed in the two treatment arms have to be compared in a standard 2-means comparison based on normal distributions. The comparison is performed two-sided in order to be on the safe side, although the hypothesis is that treatment arm 1 is more effective than treatment arm 2. Requiring a power of 90% (beta = 0.1, error of the second kind) at a significance level of 5% (alpha = 0.05, error of the first kind), the assumed parameter values result in sample sizes of *n* = 61 for each of the two treatment groups. When assuming variances of either 1 or 2 instead of 1.5 for each of the assessments, the required group sizes would be *n* = 42 or *n* = 84, respectively. In the latter case, a sample size of *n* = 63 in each group would still be sufficient for alpha = 0.05 at a power of 80% (beta = 0.2), which is often considered as sufficient in clinical trials. Thus, based on reasonable assumptions and conventional criteria, sample sizes of about 60 subjects per group should be adequate to perform this clinical intervention study successfully and to obtain a conclusive result.

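### Reading FVC from the manoeuvre with the largest FEV1+FVC sum adds a little avoidable variance to the primary variable; it does not bias the comparison between arms

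*Protocol article*

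**What the plan says.** Each spirometry session in the protocol article consists of "at least three, but no more than eight, manoeuvres", checked visually by physicians for acceptability (Lung function testing by spirometry). From these, "Spirometric indices will be taken from the manoeuvre with the largest sum of forced expiratory volume in 1 s" and FVC. The rule is stated once, with no distinction by visit, arm or bronchodilator status, and no other section gives FVC a rule of its own. The same section adds: "Specific attention will be paid to the requirement to obtain very precise and reliable lung function data".

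Under Objectives {7} the main hypothesis is that the intervention "improves lung function in terms of forced vital capacity (FVC), as an indicator of lung volume, by at least 2" per cent. Under Sample size {14}, "relative effects of m1 = 2 and of m2 = 1 are assumed for the target treatment and the control treatment group", with an "assumed variance of 1.5 for each assessment" and hence "an assumed standard deviation of about 1.7 (square root of 3) for each difference". The units of these figures are left open, and the section says that data on longitudinal variation are insufficient.

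**The concern.** FVC is a maximum: the most a participant can exhale. Under the largest-sum rule, the recorded value is the participant's best FVC only if the same curve also has the largest sum. When another curve has a sufficiently better FEV1, a smaller FVC is recorded although a larger acceptable one was achieved. Which curve is selected varies by chance from session to session, so within-session scatter in FEV1 enters the recorded FVC.

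A single-curve rule has a clear rationale for FEF25–75, which depends on the shape of one curve. The protocol gives no such reason for FVC. At stake is some precision in a trial powered on a difference of 1 unit between arms, whose own text makes precision of the spirometry a special requirement.

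**Working it through.** **1. The plan's own figure.** Inputs from Sample size {14}: difference 2 − 1 = 1, variance 1.5 per assessment, two-sided alpha 0.05, power 90%. With independent errors, the variance of the pre-post difference is 2 × 1.5 = 3. The normal-approximation formula is n per group = 2 × (1.960 + 1.282)² × SD² / difference².

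- SD rounded to 1.7: 2 × 10.51 × 2.89 = 60.7, so 61, as stated.
- SD = √3: 2 × 10.51 × 3 = 63.0, so 64 after rounding up. The gap to 61 comes from rounding the SD and has nothing to do with the present point.

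**2. Power at the planned size.** With v the variance per assessment and 60 per group, the squared standard error of the between-arm contrast is 2 × 2v/60 = v/15, so power = Φ(√(15/v) − 1.96). For v = 1.5 this is Φ(3.162 − 1.960) = Φ(1.202) = 88.5%.

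**3. What the rule adds.** The documents give no within-session SD and no correlation between FEV1 and FVC across manoeuvres. The following are therefore assumptions: FVC of 5 L, effect units read as per cent of FVC (so 1% = 50 ml and 1 %² = 2,500 ml²), within-session SD of 50 ml for both FVC and FEV1, and normal errors. For 200,000 simulated sessions per scenario, the FVC on the largest-sum curve was compared with the largest FVC. Added variance = (SD² under the sum rule − SD² under the maximum) / 2,500. Power is from step 2 with v = 1.5 + added variance, which takes 1.5 to be the variance under the largest-FVC rule.

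| Correlation | Manoeuvres | Mean shortfall (ml) | SD, largest FVC (ml) | SD, sum rule (ml) | Added variance (%²) | n per group for 90% | Power at 60 |
|---|---|---|---|---|---|---|---|
| 0.9 | 3 | 1.1 | 37.5 | 38.2 | 0.022 | 64 | 88.1% |
| 0.9 | 5 | 1.5 | 33.4 | 34.4 | 0.027 | 65 | 88.0% |
| 0.9 | 8 | 1.8 | 30.6 | 31.9 | 0.032 | 65 | 87.9% |
| 0.6 | 3 | 4.5 | 37.3 | 40.2 | 0.088 | 67 | 86.7% |
| 0.6 | 5 | 6.1 | 33.5 | 37.4 | 0.111 | 68 | 86.2% |
| 0.6 | 8 | 7.5 | 30.6 | 35.4 | 0.126 | 69 | 85.9% |
| 0.3 | 3 | 8.2 | 37.4 | 42.2 | 0.153 | 70 | 85.4% |
| 0.3 | 5 | 11.2 | 33.5 | 40.1 | 0.194 | 72 | 84.5% |
| 0.3 | 8 | 13.9 | 30.6 | 38.6 | 0.221 | 73 | 83.9% |

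One row by hand (correlation 0.6, three manoeuvres): v = 1.588, √(15/1.588) = 3.073, Φ(3.073 − 1.960) = Φ(1.113) = 86.7%. The SD of the pre-post change rises by √(1.588/1.5) − 1 = 2.9%.

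**4. Compatibility with the plan.** Under the maximum rule with three manoeuvres, within-session error contributes 37.3²/2,500 = 0.56 %², which fits inside the planned 1.5. The largest FVC was the more precise measure in every scenario tried, with normal and with left-skewed errors.

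**5. The other anchoring.** If 1.5 already describes FVC under the sum rule, the planned power includes the loss, and the change would be a gain. For the same row, v = 1.5 − 0.088 = 1.412 and Φ(√(15/1.412) − 1.96) = Φ(1.299) = 90.3%.

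**The case against.** The strongest case for leaving the rule alone is that it is explicit, set in advance and uniform, and that it keeps FVC, FEV1, their ratio and FEF25–75 on one blow. That is a legitimate design choice, and nothing in the protocol contradicts it. Its cost depends wholly on undocumented inputs, and at a correlation of 0.9 it is about half a percentage point of power. All of this stands. It limits the size of the point, but it does not give a reason to prefer the sum rule for FVC.

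Several stronger readings are tempting, and the documents do not support them:

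- **Bias in the effect.** A reader might infer that recording FVC too low distorts the result. The shortfall is one of level. One rule applies at both visits and in both arms, so its mean drops out of the change and of the contrast. Even if a participant gave 3 manoeuvres at one visit and 8 at the other, the mean shortfall at correlation 0.6 would differ by 7.5 − 4.5 = 3.0 ml, or 0.06% of 5 L.
- **FEV1 change carried into FVC.** A reader might infer that a change in FEV1 between visits would show up as a change in FVC. A shift common to all manoeuvres of a session raises every sum equally and leaves the chosen curve unchanged. A proportional 2% change in FEV1 moved mean recorded FVC by at most 0.6 ml in simulation. Only within-session scatter matters.
- **A wrong sample size.** The variance of 1.5 is an assumption tied to neither selection rule, so no error in the stated 61 follows.
- **Departure from the cited standard.** The section speaks of "In addition to strictly following ATS/ERS recommendations", but does not reproduce what they say on choosing a manoeuvre, so this cannot be judged here.

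**Conclusion.** The point holds as a minor loss of precision. The largest-sum rule lets chance variation in FEV1 help decide which FVC is recorded, and so adds avoidable variance to the primary variable at each assessment. Under the assumptions above, and taking 1.5 as the variance under the largest-FVC rule, power at 60 per group would be about 88% at correlation 0.9, 86–87% at 0.6 and 84–85% at 0.3, instead of 88.5%. The direction was the same in every scenario. The size is conditional on 5 L, on SDs of 50 ml and on a correlation that the documents do not supply. The validity of the comparison and the sample size calculation are not affected.

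**What to change.** Replace the rule with one sentence: FVC is the largest FVC and FEV1 the largest FEV1 from any acceptable manoeuvre of the session, before and after bronchodilator and at every visit; FEV1/FVC is computed from these two values, and FEF25–75 is taken from the curve with the largest sum. Alternatively, state why the single-curve rule is preferred for FVC.

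No extra tests are needed, because each session already yields at least three manoeuvres; the values of every acceptable manoeuvre must be kept. The small downside is that FVC, FEV1 and their ratio may then draw on different manoeuvres. Under Trial status the article describes recruitment as still planned, so the change could be made before any data exist; failing that, it should be made before outcomes are compared by arm.

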### Biosampling and measurements of the microbiome

The secondary outcome is considered the bacterial composition. Both saliva and gingival fluid will be collected from the participants. Gingival fluid between the teeth will be collected with sterile paper points at 6 per-protocol predetermined sites in the lower jaw (mesial and distal at the “Ramfjord” teeth 41, 44 and 36) and 6 sites in the upper jaw (mesial and distal at the “Ramfjord” teeth 21, 24, 16). The samples will be frozen directly after collection, in separate vials for the upper and lower jaw samples. Saliva will be collected as well. Subjects are asked to chew for 1 min on a paraffin gum.

### Participant timeline {13}

The time schedule of enrolment, interventions (including any run-ins and washouts), assessments and visits for participants is illustrated in the following schematic diagram (Fig. 4). From our clinical experiences, we expect a cohort of individuals with mostly good to moderate oral hygiene. To address this heterogeneity appropriately, we provide a wash-in phase with oral hygiene instructions to equalize oral health in the study population. Signs of gingivitis are mostly reversible within 2 to 4 weeks when oral hygiene is improved. Following an interim data analysis, the main study protocol is carried out.

**Fig. 4 Fig4:**
[figure not shown]
Flowchart of the study

### Sample size {14}

The calculation of the power of this study is complicated by the fact that only limited information on changes in lung function is available. The only published trial on oral sanitation and its impact on lung function included 2 × 30 subjects with severe periodontal diseases and an average age of 65.7 years. The authors reported an improvement in FEV_1_ by 3–4%predicted [70]. Whether the effect size of this study can be used to derive a reliable power calculation for our study seems questionable, mainly because of the advanced age of the study subjects and the progression of periodontal diseases in this age group. We also cannot infer whether we should expect weaker or stronger effects in our young study group with only mildconfirmed the overall association documented in a previo gingivitis, compared to the intervention in the Chinese population of older subjects. One might speculate that in our study effects would be stronger, due to a mild inflammatory status of younger subjects with gingivitis, which might be easier attenuated or abolished compared to a long-lasting inflammation accompanied by persistent structural changes of the periodont and possibly the lung. Such irreversible changes in the lung are less likely in our study, given the young age of the study subjects. As far as reversibility is concerned, the expected effect size on the lung might be even larger compared to the Chinese interventional study, given the same degree of oral inflammation. These considerations show that the power analysis has to be largely based on plausibility arguments and only partially on available data. Other types of interventions might be useful to estimate the time scale needed. For example, a complex rehabilitation programme comprising physical activity, dietary intervention and strongly monitored medication resulted in short-term improvements of FEV_1_ by 8% predicted in asthmatic patients aged 4–19 years, within an intervention period of less than 4 weeks [5]. Thus, our follow-up period might be sufficient.

Observational studies could also be used for power calculation. The few studies on oral health and lung function consistently found lower lung function in subjects with periodontitis or gingivitis. A cross-sectional study in 1463 German adults aged 25 to 86 years showed FEV_1_ values lower by 5% predicted in subjects with clinical attachment loss of more than 50%, after adjustment for several co-factors. The non-smokers showed even further lowered FEV_1_, by more than 10% predicted [22]. Similarly, a prospective follow-up study of 206 subjects (mean age 42 years) found 10% lower FEV_1_ in subjects with periodontitis [21]. The third observational study of more than 650 subjects aged 50 + years from Scandinavia reported FEV_1_ values lower by 5% predicted for subjects with poor oral health [44]. The only available population-based study in younger age (15 years) showed FEV_1_ to be lower by about 20% predicted in the approximately 10% of adolescents with the highest SBI or CPI [20]. Active smoking was uncommon at this age, and the few active smokers were excluded from this analysis. Noteworthy, all five observational studies consistently showed lower FEV_1_ in subgroups of poor oral health. Despite this, some caution is needed in the interpretation. Although some of these studies included co-variates such as smoking, socioeconomic status, chronic diseases and medication, acute infections during lung function testing and early life factors, residual confounding cannot be ruled out in view of the multiplicity of potential influencing factors. Lung function has many determinants and is varying over time. This is the reason for further interventional study in subjects of younger age. Based on the critical evaluation of the study findings on oral health and lung function, we prefer a conservative approach for our power calculation.

The power analysis focuses on the second part of the study, in which two different treatments are realized, whereby in both arms assessments before and after treatment are performed (Fig. 4). As the control treatment may be expected to be associated with a positive change, although smaller than in the target treatment group, the assumed effect is taken to be greater than zero. Thus, relative effects of m1 = 2 and of m2 = 1 are assumed for the target treatment and the control treatment group, respectively, in units that can be adapted to those of the outcome measures. There are no sufficient data on the (longitudinal) variation of measured values due to either methodological or biological sources. The power analysis is performed with an assumed variance of 1.5 for each assessment, in units identical to those of the effects and corresponding to a standard deviation (SD, square root of variance) greater than 1 but less than 1.5, which we consider as a reasonable value. Assuming that the measurement errors are independent in the pre and post-assessments, the variances add up for the pre-post differences, resulting in a total variance of each of the two differences of 3, i.e. an assumed standard deviation of about 1.7 (square root of 3) for each difference. Thus, we have two groups with expected effects of 2 or 1, both with standard deviations of about 1.7. This seems a reasonable basis for analysis, whereby the mean differences observed in the two treatment arms have to be compared in a standard 2-means comparison based on normal distributions. The comparison is performed two-sided in order to be on the safe side, although the hypothesis is that treatment arm 1 is more effective than treatment arm 2. Requiring a power of 90% (beta = 0.1, error of the second kind) at a significance level of 5% (alpha = 0.05, error of the first kind), the assumed parameter values result in sample sizes of *n* = 61 for each of the two treatment groups. When assuming variances of either 1 or 2 instead of 1.5 for each of the assessments, the required group sizes would be *n* = 42 or *n* = 84, respectively. In the latter case, a sample size of *n* = 63 in each group would still be sufficient for alpha = 0.05 at a power of 80% (beta = 0.2), which is often considered as sufficient in clinical trials. Thus, based on reasonable assumptions and conventional criteria, sample sizes of about 60 subjects per group should be adequate to perform this clinical intervention study successfully and to obtain a conclusive result.

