**Methods:**

The study has to include 120 non-smoking subjects aged between 18 and 30 years with biofilm-induced gingivitis. The chosen “waiting control group design” will compare the immediate intervention group with the delayed intervention group, which serves as a control group. Dental and gingival status, lung function and oral microbiome will be recorded. The intensified preventive intervention—professional tooth cleaning, one-stage full-mouth disinfection with CHX and safeguarding an optimal daily oral hygiene by each subject—cannot be blinded, but the outcome measurement in terms of lung function tests is blind.

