### Methods in analysis to handle protocol non-adherence and any statistical methods to handle missing data {20c}

In case of non-adherence, each individual will be contacted immediately and re-invited to follow the intended timeline. If individuals are unable to proceed with study participation, the corresponding data will be excluded from the phase 1 or phase 2 dataset (lost to follow-up).

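### The stated 61 per group for 90% power should be 63 or 64 on the plan's own variance, and the adopted 60 per group gives about 88% in the main case and 78% in the fallback case

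*Protocol article*

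**What the plan says.** All the inputs stand in the protocol article under Sample size {14}.

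- **Effects and variance.** The expected effects are 2 and 1, in units left to be adapted to the outcome. The variance is 1.5 per assessment with independent errors, "resulting in a total variance of each of the two differences of 3, i.e. an assumed standard deviation of about 1.7".
- **Test.** A normal-theory comparison of two means, "at a significance level of 5% (alpha = 0.05, error of the first kind"). On sidedness: "The comparison is performed two-sided in order to be on the safe side".
- **Power and result.** "Requiring a power of 90% (beta = 0.1, error of the second kind"), the section reports that "the assumed parameter values result in sample sizes of *n* = 61 for each of the two treatment groups".
- **Sensitivity.** For variances of 1 and 2 per assessment it gives 42 and 84 per group. For variance 2 it adds that 63 per group would give 80% power.
- **Conclusion.** About 60 per group is called adequate. The abstract fixes the total: "The study has to include 120 non-smoking subjects aged between 18 and 30 years".

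The section also admits that "There are no sufficient data on the (longitudinal) variation of measured values due to either methodological or biological sources". Under the heading on non-adherence and missing data {20c}, when someone cannot continue, "the corresponding data will be excluded from the phase 1 or phase 2 dataset".

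**The concern.** Required sample size is proportional to variance. The flanking figures of 42 (variance 1) and 84 (variance 2) therefore put the middle case (variance 1.5) at 63, yet the headline says 61. The adopted 60 is lower again. It is below 61, below 63, and below the 63 that the section itself requires for 80% power in the less favourable case. That case is what reassures the reader that the design still works if variability is higher than assumed.

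No reserve for loss is visible, since 120 is exactly 2 × 60, while the data of people who drop out are removed. A reader of a null result would take the power to be somewhat higher than it is.

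**Working it through.** **Inputs** (all from Sample size {14}): difference δ = 2 − 1 = 1; variance of the pre-post difference σ² = 1.5 + 1.5 = 3; z for two-sided 5% = 1.960; z for 90% power = 1.282; z for 80% power = 0.842.

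**Formula**, equal groups, normal approximation: n per group = 2 × (z₁ + z₂)² × σ² / δ². For 90% power, 2 × (1.960 + 1.282)² ≈ 21.015 (unrounded z values), so n = 21.015 × σ².

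**Reproducing 61.** With the SD cut to 1.7, σ² = 2.89 and n = 21.015 × 2.89 = 60.73, hence 61. Other readings do not give it: a t-test with SD 1.7 gives 61.7, and a one-sided test gives 49.5.

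**With the stated variances, unrounded:**

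| Variance per assessment | σ² of difference | Power | n computed | n stated |
|---|---|---|---|---|
| 1 | 2 | 90% | 42.03 | 42 |
| 1.5 | 3 | 90% | 63.04 | 61 |
| 2 | 4 | 90% | 84.06 | 84 |
| 2 | 4 | 80% | 62.79 | 63 |

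Three of the four figures follow from unrounded variances, rounded to nearest. Only the headline figure does not. It should be 63 by that convention and 64 if rounded up. A t-test needs 64.02, so 65.

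**Power at 60 per group, nobody lost**, from power = Φ(δ / √(2σ²/n) − 1.960):

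- Main case: √(2 × 3 / 60) = 0.3162; 1 / 0.3162 = 3.162; Φ(1.202) = 88.5%. A t-test gives 88.0%.
- Fallback (variance 2): √(2 × 4 / 60) = 0.3651; 1 / 0.3651 = 2.739; Φ(0.779) = 78.2%. A t-test gives 77.5%.

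At the stated 61 per group with σ² = 3, power is 89.0% (normal).

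**Effect of loss, illustration only.** The article gives no loss rate. If 10% were lost equally from both arms after allocation, 60 × 0.9 = 54 per group would remain:

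- Main case: √(6 / 54) = 0.3333; Φ(3 − 1.960) = 85.1% (t-test 84.4%).
- Fallback: √(8 / 54) = 0.3849; Φ(2.598 − 1.960) = 73.8% (t-test 73.1%).

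**The case against.** The error is small and its source is in plain view. The section gives the SD as approximately 1.7 and the group size as approximately 60. The shortfall is 1.0 point at 61 per group and 1.5 to 1.8 points at 60 by the normal method that it names. Its own sensitivity range, 42 to 84, dwarfs a difference of two or three per arm. A slight positive correlation between pre and post errors (0.05, say, as an assumption) would cut the variance to 2.85 and the required n to 59.9. All of this limits the importance of the point. None of it makes 61 the right answer to the inputs stated, which include independence and a variance of 3.

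Three stronger readings are tempting, and the article does not support them.

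- *That it claims 90% power for 120 subjects.* It attaches 90% to 61 per group and 80% to 63 per group. Of about 60 it says only that this should be adequate.
- *That attrition makes the trial seriously underpowered.* No loss rate is given. The power analysis concerns the second part of the study, and groups are formed after the wash-in (Interim analyses {21b}), so wash-in losses need not shrink the allocated groups. The article does not say at which stage the 120 are counted, and a condensed article may omit an allowance that the full protocol contains. What stands is that the section shows none and that losses after allocation are excluded.
- *That the assumed SD is far too small.* The article gives no spirometric variability against which to judge it. It admits the gap and varies the variance. Power computed at larger SDs would rest on invented figures.

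**Conclusion.** The stated 61 is wrong on the section's own inputs. The correct figure is 63 under its own rounding, 64 rounded up, or 65 with a t-test. The adopted 60 per group reaches neither that figure nor the stated 63 for the fallback. With all 120 analysed, power is about 88% (88.5% normal, 88.0% t-test) in the main case and about 78% (78.2% and 77.5%) at variance 2. That is about 1.5 to 2.5 points below 90% and 80%.

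These results assume the stated difference of 1, independent pre and post errors, and equal groups. Power falls further with any loss after allocation, but by how much cannot be read from the article. This is a modest correction to a published figure. It does not show that the design is unsound, and eligibility, allocation, endpoint and analysis are unaffected.

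**What to change.** - In Sample size {14}, replace 61 with 63 (or 64, rounding up), computed from the variance of 3 and not from a rounded SD.
- Keep 120. In place of the statement that about 60 per group is adequate, give the power delivered: about 88% at variance 1.5 and about 78% at variance 2 with no loss, and lower after exclusions. If a loss rate is expected, state it with the matching power.
- Express effect and SD in % of FVC. The units are now left open, and the Discussion ties the power calculation to FEV1 and FEF25–75 although Objectives {7} make FVC the main outcome.
- If the SD is to be checked blind, use the phase 2 pre-post differences pooled over arms. A single spirometry before allocation would give the spread between subjects, which is not the quantity in the calculation, and the article does not show that such data are collected.

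The cost is a few reworded sentences with slightly less favourable figures. No participants or visits are added.
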